## Selection of comparison groups/controls

For the second phase of this study, we aim to compare the clinical outcomes of patients with NVAf prescribed OACs and who were not prescribed OACs. This will be done by including incident cases of NVAf identified from phase one cohort from 2009 to 2019 and further divide them into two groups; cases are patients treated with OACs within one year of NVAf diagnosis and controls are those who did not receive OACs for  $\geq 1$  year after NVAf diagnosis. Many confounders will be controlled for when evaluating the effect of treatment (OACs) on the clinical outcomes of interest (i.e. stroke, bleeding, or all-cause mortality). Potential confounders are likely to include patient age, sex, and presence of hypertension, diabetes, coronary artery disease, heart failure, kidney disease, liver disease, peripheral artery disease, fall risk, history of stroke or bleeding, malignancy, anaemia, alcohol abuse, antiplatelet use or non-steroidal anti-inflammatory drugs. At first, we aim to perform propensity score matching method using a multivariable logistic regression model that contains the confounders mentioned above to estimate patient's probability to receive OACs. Matching will operate by taking each case and finds the closest propensity score match among controls, within a predetermined caliper bandwidth. However, in case if the matching method failed to achieve balance among the two patient groups or caused substantial exclusion of individuals from the main cohort, then we will consider overlap propensity score weighting. By applying overlap propensity score weighting each patient's will be weight by the probability of that patient being assigned to the opposite treatment group.

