**Outcomes:**

The primary outcomes will be the prescription of OACs either VKA or NOACs, product codes for OACs are described in (Appendix 2). Status of anticoagulation therapy will be classified as either OAC prescribed or OAC not prescribed. OAC prescription will be defined as the presence of any OACs prescription during the study period. Treatment patterns for OACs users will be evaluated for (1) continuous exposure to OACs: no treatment change until end of follow-up period, defined starting from the date of first prescription to the intended duration of that prescription, plus the duration of any overlapping and successive prescriptions of the same drug within 30 days after the expected end of a prescription. For VKAs, INR measurements if available will be treated as indicator for VKA exposure and therefore treated in the same way as prescriptions; (2) OACs discontinuation: no OACs prescription after a period of therapy without resumption of OACs; (3) OACs switch: this will include four switching categories: from antiplatelet only to OACs, from VKA to NOAC, from NOACs to VKA, and between NOACs switches. OACs not prescribed will be defined as no prescription record of an OACs at any time after NVAf diagnosis, this will also include patients prescribed lone antiplatelet therapy. Proportions of patients prescribed antiplatelets such as aspirin or other antiplatelets (i.e., clopidogrel, ticagrelor, or prasugrel) within the study period will be described for both OACs exposed and not exposed patients. Products codes of antiplatelet agents can be found in (Appendix 2).

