## 2. Phase 2 - Comparative study

**Exposures:** In this cohort, prescriptions for OAC will determine patient’s exposure status. NVAf patients identified from phase one and who have received a continuous prescription of either VKAs or NOACs within one year of NVAf diagnosis will be in the OACs “exposed group”. While “OACs unexposed” patients are individuals in phase one who haven’t received a prescription for anticoagulation therapy and remained OACs free for  $\geq 1$  year from NVAf diagnosis.

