2. Phase 2 – Comparative study: For comparison of demographic variables and comorbidities among OACs treated and not treated individuals, independent sample t tests will be used for numeric variables, while Chi squared  $\chi^2$  tests or Fisher exact tests will be used for categorical variables. To control for imbalances in patient characteristics between cohorts, we will calculate an exposure-specific propensity score as the predicted probability of receiving OACs conditional upon individuals baseline covariate (as described in section M) using logistic regression models. Then we will consider applying propensity score matching methods to match each OACs unexposed controls to up to 5 NVAF OACs exposed cases using a calliper of 0.2 standard deviation (SD) of the propensity score logit. After matching, Cox regression will be used to compute hazard ratios (HRs) of the outcomes of interest, comparing exposure to OACs versus no OACs. Initially crude HRs will be obtained, then stratified by type of OACs (i.e., VKAs and NOACs) and adjusted for age, and other important covariates described in section N. In this phase immortal time bias would occur due to the definition of exposure, where in the time from AF diagnosis till receipt of OACs those in the “OACs prescribed group” cannot have the outcome by design, otherwise they would have been classified as non OAC users. To avoid the problem of immortal time bias, we will consider using time-varying exposures, where in a survival analysis, the time period previous to the index date of OACs initiation is reclassified as nonuser for those in the “OACs prescribed group”.

3. Phase 3 – Major bleeding events cohort: At first, we will use descriptive statistics to present the overall characteristics of this cohort who have experienced major bleeding events while taking OACs. After that patients will be divided to 2 groups one for the patients who resumed anticoagulation after the index major bleeding event and the other for the group who remained OACs free and will compare the patient characteristics between the two groups using Chi squared  $\chi^2$  tests, Fisher's exact tests, and analysis of variance, as appropriate. Survival (time-to-event) models will be constructed to compare the time between the indexed major bleeding to the earliest event of stroke, bleeding, or all-cause mortality considering if patients were restarted on OACs or not. In Cox models we will control for age, time to OACs resumption, CHA2DS2-VASc

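### Phase 2 states when OAC exposure starts but not when it ends or changes drug class, and its definitions of the exposed group disagree

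*Protocol*

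**What the plan says.** All references are to the protocol.

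- *Data/statistical analysis*, Phase 2, raises immortal time bias and says "we will consider using time-varying exposures". The only rule it then gives is that, for patients in the OAC group, "the time period previous to the index date of OACs initiation is reclassified as nonuser".
- The same paragraph plans hazard ratios by drug class: "Initially crude HRs will be obtained, then stratified by type of OACs (i.e., VKAs and NOACs").
- Phase 2 *Outcomes* counts events throughout follow-up and sets no on-treatment window.
- *Selection of comparison groups/controls* defines the treated group by start alone: "cases are patients treated with OACs within one year of NVAf diagnosis".
- Phase 2 *Exposures* asks for more: patients who "received a continuous prescription of either VKAs or NOACs within one year of NVAf diagnosis". Continuity is not defined there.
- Phase 1 *Outcomes* does define continuous exposure: "no treatment change until end of follow-up period, defined starting from the date of first prescription to the intended duration of that prescription". Later supplies of the same agent extend the episode if the gap is no more than 30 days. The section also defines discontinuation and four kinds of switch, and lets INR measurements stand in for VKA prescriptions. All of these are presented as Phase 1 treatment patterns.

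**The concern.** A time-varying exposure needs a start, an end and a rule for changes of state. Phase 2 supplies the start only. Aim 4 asks for the effect of OAC prescribing on stroke, bleeding and death. Cases accrue from January 2009 to June 2019, so follow-up can reach about ten years. The protocol expects VKA-to-NOAC switching in that period, since Phase 1 will report it year by year, and its secondary bleeding outcome includes bleeds that lead to stopping.

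If later off-drug time stays in the exposed group, both the stroke benefit and the bleeding harm probably move towards no effect. If time after a switch stays with the first drug, the VKA and NOAC hazard ratios move towards each other. A reader could not then tell a weak drug effect from diluted exposure. If stoppers and switchers are left out instead, exposed patients are chosen by what happened to them after follow-up began.

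**Working it through.** **1. The definitions side by side.** Take a patient who starts a VKA in 2011 within a year of diagnosis, moves to a NOAC in 2015 and stops in 2017.

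| Section | Exposed? | Time after 2015 and after 2017 |
|---|---|---|
| *Selection of comparison groups/controls* | Yes | Not addressed |
| Phase 2 *Exposures*, continuity confined to the first year | Yes, if continuous in that year | Not addressed |
| Phase 2 *Exposures*, with the Phase 1 meaning of continuity | No, because treatment changed | Patient is in neither group: not continuous, yet not OAC-free for a year |
| *Data/statistical analysis*, Phase 2 | Non-user before the start, user after it | Not addressed |

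**2. Cross-check with Phase 3.** Phase 3 takes the Phase 2 exposed patients who had a major bleed. It compares those who resumed OAC with those who stayed off it, and it describes switches after the bleed. An exposed group limited to patients with no treatment change to the end of follow-up would not contain those groups, unless follow-up for this purpose ends at the bleed, which is not stated. The secondary outcome that counts bleeds leading to discontinuation also needs stoppers in the cohort.

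**3. The protocol's own figures.** *Sample size considerations* uses yearly stroke rates of 8% without OAC and 2.8% on warfarin. 8/2.8 = 2.86 (stated as 2.8), and the inverse is 2.8/8 = 0.35. A two-proportion formula with a simple-average pooled proportion of (0.08 + 0.028)/2 = 0.054, two-sided 0.05, 80% power and 5:1 allocation gives 193 unexposed and 5 × 193 = 965 exposed, close to the stated 194 and 970. The inputs are therefore read as intended. The point does not depend on the sample size.

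**4. Dilution if exposure is carried forward.** Let f be the share of exposed person-time that is off drug. The documents give no value for f, so it is assumed, and off-drug time is assumed to carry the untreated rate.

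Observed ratio = [(1 − f) × 2.8 + f × 8] / 8

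- f = 0: 2.80/8 = 0.35
- f = 0.15: (2.38 + 1.20)/8 = 3.58/8 = 0.45
- f = 0.30: (1.96 + 2.40)/8 = 4.36/8 = 0.55
- f = 0.50: (1.40 + 4.00)/8 = 5.40/8 = 0.68

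**5. Drug class if time after a switch stays with the first drug.** For illustration only, assume hazard ratios against no OAC of 0.35 for VKA and 0.25 for NOAC, a true NOAC/VKA ratio of 0.25/0.35 = 0.71. Let g be the share of VKA-labelled time actually spent on a NOAC.

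- g = 0.10: VKA appears as 0.34, and 0.25/0.34 = 0.74
- g = 0.30: VKA appears as 0.32, and 0.25/0.32 = 0.78
- g = 0.50: VKA appears as 0.30, and 0.25/0.30 = 0.83

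**6. Power is not the issue.** *Feasibility counts* expects about 14,000 untreated patients. With that number and at least as many exposed, power stays near 100% at every f up to 0.50. The result would be a precise but diluted estimate.

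**The case against.** A reader might infer that the protocol keeps patients exposed for ever after their first OAC and charges later events to that drug. The documents do not say so. The Phase 2 rule was written to deal with immortal time, is offered only as something to consider, and is silent on what follows initiation. Silence is not a rule. The word continuous in Phase 2 *Exposures* could even remove stoppers and switchers, and then there would be no off-drug time to dilute anything. That objection stands against the stronger reading, but it exchanges one bias for another and fits poorly with Phase 3.

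It can also be said that the end of exposure, grace periods and handling of switches are commonly left to an analysis plan, which is not shown here. That would answer a mere omission. It does not answer sections that disagree on who is in the exposed group, or drug-class hazard ratios promised with no consistent place for switchers.

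Aim 4 concerns prescribing, so an as-started contrast is legitimate. This stands, and is a reason to report that analysis too.

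A reader might also infer that strokes after a bleed-driven stop are generally counted against OAC. For the primary composite this is weak. Major bleeding is itself a component, so a first-event analysis would already have counted the bleed, and the discontinuation wording belongs to the secondary, non-major bleeding outcome.

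Finally, if stopping is linked to illness, off-drug patients need not have the untreated rate, so neither the size nor the direction of the dilution is assured.

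**Conclusion.** The point holds in this form: Phase 2 fixes the start of exposure but no end and no reassignment at a class switch, and its sections give incompatible conditions for entering the exposed group. Carrying exposure forward probably dilutes the OAC effect and draws the VKA and NOAC hazard ratios together. Importing the Phase 1 definition selects the exposed group on future treatment, a bias to which the documents allow no figure to be put.

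The range of 0.45 to 0.68 in place of 0.35 illustrates the first case only. It rests on assumed off-drug shares of 15% to 50%, on the untreated rate applying once the drug is stopped, and on exposure being carried forward, which the protocol neither states nor excludes. The drug-class figures rest on assumed hazard ratios and switching shares. The matter should be corrected before analysis.

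**What to change.** 1. Reconcile *Selection of comparison groups/controls*, Phase 1 *Outcomes*, Phase 2 *Exposures* and the Phase 2 part of *Data/statistical analysis*, so that entry to the exposed group depends on OAC initiation and not on later continuity.
2. In *Data/statistical analysis*, commit to a time-updated exposure with three states (no OAC, VKA, NOAC) built from the Phase 1 episodes, with that section's own 30-day gap and INR provision. The state changes at a class switch and returns to no OAC at discontinuation. A change from one NOAC to another stays in the NOAC state, and a patient who resumes re-enters the state for the class resumed.
3. Use these states for the VKA and NOAC hazard ratios.
4. Report beside it the as-started analysis, with exposure carried forward from the first OAC.

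The cost is protocol wording and extra programming. No new data are needed, because Phase 1 already requires the stop and switch dates. The drawback is that the time-updated estimate can be distorted by stopping prompted by illness. Showing both analyses lets the reader see how far the answer depends on the exposure definition.

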Earlier studies have shown that anticoagulation therapy based on guideline risk stratifications is associated with a 60%–70% reduction in thromboembolic events and mortality. However, there is still room to improve risk stratification of patients with AF and anticoagulation. Recently, the Global Anticoagulant Registry in the FIELD-Atrial Fibrillation (GARFIELD-AF) model was developed and it allows the simultaneous prediction of stroke, bleeding, and mortality. This model is not a risk score that categorizes patients into risk groups, but instead it provides a risk prediction on a continuous scale. After external validation of the model in a Danish cohort, the GARFIELD-AF model was superior to CHA2DS2-VASc in predicting stroke/SE and comparable with HAS-BLED for predicting major bleeding. Due to the novelty of this risk prediction tool, further studies are needed to demonstrate its ability to accurately stratify AF patients based on their risk of stroke, bleeding, and mortality to promote informed decision-making to prescribe OACs.

Another contributing factor to the under-prescription of OACs in AF patients is history of major bleeding events during anticoagulation therapy. A meta-analysis of observational studies that evaluated the effect of reinitiating OACs on bleeding recurrence and thromboembolic events found a reduction in the risk of thromboembolism and all-cause mortality, without increasing recurrence of bleeding. Since randomized controlled trials (RCTs) that tested OACs, have excluded patients with previous intracranial haemorrhage (ICH), the timing to reinitiate OACs after ICH has not been systemically studied, and varies widely in observational studies from (72 hr to 30 weeks) reflecting lack of consensus. Moreover, of the available bleeding risk scores, the HAS-BLED score has been validated to predict ICH and recurrent ICH after first spontaneous ICH. However, it remains unclear if other risk assessment scores for stroke and bleeding hold similarly in these high-risk individuals and if they could be used to inform

decision-making for reinitiating OACs in these patients.

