### **Plan for addressing confounding**

In phase 2, we aim to conduct a comparison between NVAF patients who were exposed to OACs (cases) and patients who were not exposed to OACs (controls). We will calculate an exposure-specific propensity score as the predicted probability of receiving OACs conditional upon the effect of potential confounders (described in section M). Then we will use a propensity score matching method to achieve similarity of measured confounders across cases and control groups. When estimating HRs using Cox regression models for the outcomes of interest among patient groups, we will also adjust for age, sex, IMD, stroke risk, bleeding risk, frailty, Charlson comorbidity index, and prescription of antiplatelets.

In phase 3, when looking at the predictors of restarting OACs after the indexed bleeding events we will take in account many confounders that could influence this decision, this will be done by using a multinomial logistic regression to adjust for the covariates described in section N. These covariates will also be considered when conducting survival analysis to compare the time between the indexed major bleeding to the earliest event of stroke, bleeding, or death among patients who restarted OACs and those who did not. Also, when evaluating the outcomes of restarting OACs we will consider the timing of restarting anticoagulation after bleeding, and stratify patients based on different time periods of OACs reinitiating.

In both phase 2 and 3, an additional analysis will be considered to assess the robustness of results to unmeasured confounding using the E-value methodology. This estimates what the relative risk would have to be for any unmeasured confounder to overcome the observed association of OACs prescribing with the clinical outcomes of stroke, bleeding, or mortality.

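### Phase 3 classes patients by later OAC resumption but counts time from the index bleed, which biases mortality in favour of resumption; for stroke and rebleeding the direction depends on a rule the protocol does not state

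*Protocol*

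**What the plan says.** The Phase 3 paragraph of Data/statistical analysis fixes four things.

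- **Groups:** "patients will be divided to 2 groups one for the patients who resumed anticoagulation after the index major bleeding event and the other" for those who stayed off OACs.
- **Clock and endpoint:** the models "compare the time between the indexed major bleeding to the earliest event of stroke, bleeding, or all-cause mortality considering if patients were restarted".
- **Covariates:** "In Cox models we will control for age, time to OACs resumption, CHA2DS2-VASc" and further risk, comorbidity and frailty scores.
- **Timing of restart:** Plan for addressing confounding adds that the team will "stratify patients based on different time periods of OACs reinitiating".

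That section also restates the survival contrast, as time to the "earliest event of stroke, bleeding, or death among patients who restarted OACs and those who did not". The two-group split is therefore part of the outcome comparison and not only descriptive.

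Immortal time is discussed once, in the Phase 2 paragraph: "In this phase immortal time bias would occur due to the definition of exposure". The remedy follows there: "To avoid the problem of immortal time bias, we will consider using time-varying exposures", with time before OAC initiation counted as non-use. The protocol gives Phase 3 no time-varying exposure, landmark or later time origin.

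**The concern.** The groups are defined by something that happens after time zero. Person-time between the bleed and the restart is credited to the resumed group, although a patient who dies in that interval can only be counted as OAC free. Deaths before restart therefore all fall on one side, while the matching survival time falls on the other.

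Aim 5 asks how outcomes after a major bleed relate to resumption and to its timing. Study type calls Phase 3 hypothesis testing, and mortality is among its primary outcomes. An apparent survival benefit of restarting, or of restarting later, could come from the time accounting alone.

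**Working it through.** **1. Inputs.** The protocol gives no event rate, resumption share, restart-time distribution or target hazard ratio for Phase 3, so there is no figure to reproduce. The only delay it mentions is for intracranial haemorrhage, where timing "varies widely in observational studies from (72 hr to 30 weeks". Everything below is assumed: 60% intend to resume, restart times are exponential with a mean of 1 or 3 months, follow-up is 2 years, and resumption has no effect (true ratio 1.00).

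**2. One case by hand.** Event hazard λ = 0.3/yr, restart rate ρ = 4/yr (mean 3 months), a = λ + ρ = 4.3, τ = 2. Only restarts before the event count. Per patient:

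- Everyone: event probability 1 − e^(−0.6) = 0.4512; person-years 0.4512/0.3 = 1.5040.
- Among intenders, restart and then event: 0.4512 − (0.3/4.3)(1 − e^(−8.6)) = 0.4512 − 0.0698 = 0.3814.
- Among intenders, person-years from the bleed for those who restart: 1.5040 − {λ[1/a² − e^(−aτ)(τ/a + 1/a²)] + τe^(−aτ)} = 1.5040 − 0.0166 = 1.4874.
- Resumed group: 0.6 × 0.3814 = 0.2289 events over 0.6 × 1.4874 = 0.8924 person-years, or 0.256/yr.
- OAC-free group: 0.4512 − 0.2289 = 0.2223 events over 1.5040 − 0.8924 = 0.6116 person-years, or 0.364/yr.
- **Rate ratio as planned: 0.256/0.364 = 0.70.**

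Now count time before restart as off OAC. An intender's pre-restart time is (1 − e^(−8.6))/4.3 = 0.2325 person-years, which leaves 1.5040 − 0.2325 = 1.2715 on OAC.

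- On OAC: 0.3814/1.2715 = 0.300/yr.
- Off OAC: 0.2223/(1.5040 − 0.6 × 1.2715) = 0.2223/0.7411 = 0.300/yr.
- **Rate ratio: 1.00.**

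**3. Range.** Simulated crude rate ratios, 1,000,000 patients per scenario, truth 1.00:

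| Hazard | Mean restart | Restart must precede event | Later restarts count, 20–40% of first events fatal |
|---|---|---|---|
| Constant 0.1–0.5/yr | 3 months | 0.69–0.73 | 0.86–0.93 |
| Constant 0.1–0.5/yr | 1 month | 0.86–0.90 | 0.94–0.98 |
| 1.0/yr for 3 months, then 0.3–0.5/yr | 3 months | 0.50–0.57 | 0.76–0.89 |
| 1.0/yr for 3 months, then 0.3–0.5/yr | 1 month | 0.72–0.77 | 0.87–0.96 |

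If later restarts count and no first event is fatal, the ratio is 1.00.

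**4. Cox models.** A separate simulation had 24 scenarios of 12,000 patients and a true hazard ratio of 1. Assumptions were 0.1, 0.2 or 0.4 events/yr, constant or three times higher in the first 90 days; 50% or 70% intending to resume; and restart uniform from 3 days to 12 or 30 weeks. Only restarts before the event counted.

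| Model | Hazard ratio |
|---|---|
| Fixed groups, clock from the bleed | 0.39–0.90 |
| Plus time to resumption, coded 0 for non-resumers | 0.56–0.96 |
| Plus time to resumption, mean-centred | 0.39–0.90 |
| Time-varying resumption | 0.93–1.10 |
| 90-day landmark | 0.91–1.10 |

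The last two rows centre on 1; their spread is simulation noise.

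**5. Stratifying by restart interval.** With hazard 0.3/yr, a 3-month mean and restart required before the event, the ratios against non-resumers are 0.81 (under 30 days), 0.74 (30–90 days), 0.65 (90 days to 6 months) and 0.48 (over 6 months). This trend favouring later restart is false, because timing has no effect in the simulation.

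**The case against.** The best counter-argument is that the text does not require a resumer to be free of non-fatal events before restarting. Read literally, a patient who has a stroke, survives and then restarts has resumed. Under that reading the Cox simulation gave hazard ratios of 0.98 and 1.00 in the two scenarios run. If a stroke tends to prompt a restart, the bias could run the other way. This stands. A reader might infer that resumption will look protective for every outcome, but the protocol supports that direction only for death.

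Two further inferences go too far. One is that adjusting for time to resumption creates the bias. The Cox results show that it leaves the bias unchanged or reduces it. The valid criticism is that the variable has no value for non-resumers, is post-baseline for resumers, and does not cure the problem. The other is that recorded restarts are necessarily late. Limitations of study design says only that some in-hospital restarts might go unseen.

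It might also be said that the details belong in a statistical analysis plan. That does not answer the point, because the protocol itself fixes the grouping, time origin, endpoint and covariates that together produce the bias. The planned E-value analysis concerns unmeasured confounding and does not address misallocated person-time.

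**Conclusion.** The concern holds in this form. The Phase 3 comparison as written is biased in favour of resumption for all-cause and cardiovascular mortality, because survival to restart is a condition of being classed as resumed. For stroke and rebleeding the direction turns on whether a restart after a first non-fatal event counts, and the protocol leaves that open. Nothing planned for Phase 3 removes the bias. Stratifying by observed restart interval does not, since later strata carry more guaranteed survival.

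The size rests wholly on assumed rates and restart times. The crude ratios of 0.50 to 0.90 and 0.76 to 0.98 are illustrations, not predictions. Quoting only the strongest scenarios would overstate what is known. In the scenarios with a high early hazard, crude ratios also mix periods of different risk; the Cox models align time since the bleed and still show the bias. Because Aim 5 depends on this comparison and the protocol already describes the remedy for Phase 2, it should be corrected before analysis.

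**What to change.** - Carry the Phase 2 time-varying exposure into Phase 3 as a firm commitment. Count every patient as off OAC from the index bleed and as resumed from the first post-bleed OAC prescription. Fit it in a Cox model with time since the bleed as the time scale.
- State that a restart after the first outcome event does not define exposure for that event.
- Remove time to resumption from the Cox covariates.
- For the timing question, replace stratification by observed restart interval with landmark analyses among patients alive and event-free at the landmark, for example at 30, 60 and 90 days. Clone-censor-weighting is an optional alternative.

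The cost is revised wording and modest programming, with no new data. Landmark analyses lose patients whose events come earlier. Any unseen in-hospital restarts would still misclassify some time as off OAC, so that limitation should stay in the text.

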**Covariates:**

- Patients' demographic information (age, gender, ethnicity, body mass index (BMI), geographic location (rural vs. urban), smoking status, alcohol consumption, Charlson comorbidity index for the severity of comorbidity (Appendix 3 and 4), electronic frailty index (eFI), and the index of multiple deprivation (IMD).
- Clinical covariates such as CHA2DS2-VASc, GARFIELD-AF, HAS-BLED, and HEMORR2HAGES risk assessment scores all at the time of the index haemorrhage event.

- Anatomic location of the index MB event will be identified and classified according to the critical site of bleeding (i.e., intraspinal, intracranial, intraocular, intra-articular, pericardial or other bleeding sites).

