score and HAS-BLED score, Charlson comorbidity index, and eFI. In a secondary analysis, we will group patients who resumed OACs according to the type of anticoagulation drug used after the indexed bleeding events and compare the outcomes using Cox models in a similar manner. We will assess the proportional hazards assumption by examining Schoenfeld residuals and confirming that it is not violated. To identify variables independently associated with resuming

OACs after the indexed bleeding event multivariate logistic regression models will be used and fitted with the covariates described in section N. All the statistical analyses will be carried out using STATA (version 16).

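### The Phase 3 Cox models are given a six-variable adjustment set without index bleed site in one section and a wider, uncommitted set with site in another, so the resumption hazard ratio may be confounded by site

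*Protocol*

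**What the plan says.** Protocol, Data/statistical analysis, item 3 (Phase 3), describes survival models for the time from the index major bleed to the earliest of stroke, bleeding or death, by whether anticoagulation was restarted. It then names the adjustment variables: "In Cox models we will control for age, time to OACs resumption, CHA2DS2-VASc" "score and HAS-BLED score, Charlson comorbidity index, and eFI". That makes six.

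Protocol, Plan for addressing confounding, deals first with predictors of restarting, where "we will take in account many confounders that could influence this decision" and "this will be done by using a multinomial logistic regression to adjust for the covariates described in section N". It continues: "These covariates will also be considered when conducting survival analysis to compare the time between the indexed major bleeding to the earliest event". This is the same endpoint and the same contrast.

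The Phase 3 covariates, under Exposures, outcomes and covariates, include bleed site: "Anatomic location of the index MB event will be identified and classified according to the critical site of bleeding". The categories given there are intraspinal, intracranial, intraocular, intra-articular, pericardial and other. Outcomes to be measured lists seven critical sites in its major bleeding definition: these five plus intramuscular and retroperitoneal.

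**The concern.** Two sections describe the covariates of one model and do not agree. The section that commits to a set leaves out bleed site. The section that brings site in does not commit to it. Study type calls Phase 3 hypothesis testing, so the adjustment set should not be open to choice once results can be seen.

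Site matters because the protocol treats the Phase 3 covariates as confounders of the decision to restart, and the model for predictors of resumption is to be fitted with them. Site would then enter the model for restarting but not the named model for outcome. Study background also says that restart timing after intracranial haemorrhage varies widely and lacks consensus. If site influences restarting and also influences stroke, rebleeding or death, leaving it out mixes the effect of site with the effect of resumption.

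A smaller point concerns the categories. Retroperitoneal and intramuscular bleeds meet the protocol's definition of a critical site, but the Phase 3 grouping places them in the residual category with non-critical bleeds.

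**Working it through.** **1. The two sets compared.**

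| Phase 3 covariate | Named in analysis section | In Phase 3 covariate list |
|---|---|---|
| Age, CHA2DS2-VASc, HAS-BLED, Charlson, eFI | yes | yes |
| Time to resumption | yes | no |
| Index bleed site | **no** | **yes** |
| Sex, ethnicity, BMI, rural/urban, smoking, alcohol, IMD | no | yes |
| GARFIELD-AF, HEMORR2HAGES | no | yes |

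**2. Do the six variables capture site?** Every Phase 3 patient has had a major bleed, so the bleeding item of HAS-BLED does not separate sites. Its stroke item might do so in part, and time to resumption may correlate with site. Neither is site itself.

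**3. Illustrative size.** The protocol has no figure to reproduce. All inputs below are assumptions: intracranial share π; probability of restarting r₁ (intracranial) and r₀ (other); yearly death rates λ₁ and λ₀. The true effect of resumption is set to 1.00, follow-up is one year, and death times are exponential.

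- Intracranial share in resumers: a = πr₁ / [πr₁ + (1−π)r₀]
- In non-resumers: b = π(1−r₁) / [π(1−r₁) + (1−π)(1−r₀)]
- Rate in a group with share p: [p(1−e^−λ₁) + (1−p)(1−e^−λ₀)] / [p(1−e^−λ₁)/λ₁ + (1−p)(1−e^−λ₀)/λ₀]

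Middle scenario: a = 0.06/0.54 = 0.111 and b = 0.14/0.46 = 0.304. With λ₁ = 0.45 and λ₀ = 0.15, resumers have 0.1641/0.9149 = 0.179 deaths per year and non-resumers 0.2072/0.8911 = 0.233. The ratio is 0.77.

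| π | r₁ vs r₀ | λ₁ vs λ₀ | a vs b | Crude ratio, death | Crude ratio, composite |
|---|---|---|---|---|---|
| 15% | 40% vs 60% | 0.30 vs 0.15 | 0.105 vs 0.209 | 0.92 | 0.95 |
| 20% | 30% vs 60% | 0.45 vs 0.15 | 0.111 vs 0.304 | 0.77 | 0.86 |
| 25% | 25% vs 65% | 0.60 vs 0.15 | 0.114 vs 0.417 | 0.61 | 0.74 |

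The composite column adds an assumed 0.15 per year of stroke or bleeding, unrelated to site, to both rates.

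**4. Cross-check with the binary-confounder bias factor.** The formula is [1 + p₁(g−1)] / [1 + p₀(g−1)], where p₁ and p₀ are the intracranial shares in resumers and non-resumers and g is the hazard ratio of site on outcome.

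| p₁ vs p₀ | g = 1.5 | g = 2 | g = 3 |
|---|---|---|---|
| 20% vs 20% | 1.00 | 1.00 | 1.00 |
| 15% vs 25% | 0.96 | 0.92 | 0.87 |
| 10% vs 30% | 0.91 | 0.85 | 0.75 |
| 10% vs 40% | 0.88 | 0.79 | 0.67 |

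With g = 1 every entry is 1.00. If intracranial bleeders restarted more often rather than less, the factor would exceed 1.

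**5. What these figures are not.** They are crude ratios. None of the six variables is adjusted for, so they do not measure residual bias in the named model.

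**The case against.** The best defence reads the two sections together. The analysis section does not say that only those six variables will be used, and the confounding section is additive: six core variables, with the Phase 3 covariates, including site, as candidates. The baseline comparison of resumers and non-resumers could also reveal an imbalance in site. On this reading the plan allows for site, and final covariate detail may sit in an analysis plan that is not shown.

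Part of this stands. A reader might infer that the plan excludes site and so leaves the hazard ratio confounded; the documents do not support that, because the confounding section leaves room for site. A reader might also infer that the confounding section requires the whole covariate list; it says only that the covariates will be considered. Nor does the protocol say that intracranial bleeders restart less often or fare worse. Study background reports uncertainty about timing after intracranial bleeding and does not compare sites. The claim that nothing in the named set reflects site would also be too strong, given the HAS-BLED stroke item.

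What the defence does not remove is the mismatch. One section commits to a list, the other widens it without commitment, and the choice stays open. This is more than detail deferred to an analysis plan, because the protocol itself states a set. The planned E-value analysis addresses unmeasured confounding and does not replace adjustment for a covariate that is already to be identified.

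**Conclusion.** The inconsistency is established from the text. The bias is a risk that depends on which section the analyst follows. If the six-variable set is used, the resumption hazard ratio may be confounded by bleed site to the extent that site affects both restarting and outcome. If intracranial bleeds are restarted less often and do worse, resumption would look more favourable than it is.

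The range of about 0.92 to 0.61 under no true effect rests wholly on assumed inputs, for death alone and without adjustment. The lowest value needs a fourfold death rate in a quarter of the cohort. The range narrows to about 0.95 to 0.74 under the composite assumption shown, and would narrow further if the named covariates partly capture site. The site-category mismatch is minor: such bleeds still enter the cohort through the major bleeding definition, and only their grouping changes. The correction should be made because it is nearly free and the protocol itself treats site as a possible confounder of the restart decision.

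**What to change.** - Reconcile the Phase 3 paragraph of Data/statistical analysis with Plan for addressing confounding, so that both state one pre-specified Cox covariate set that includes index bleed site. State for each remaining Phase 3 covariate whether it is in or out.
- Align the Phase 3 site categories with the seven critical sites in Outcomes to be measured, so that retroperitoneal and intramuscular bleeds are not pooled with non-critical bleeds.
- Optionally, stratify the baseline hazard by site group (for example intracranial, other critical, non-critical) instead of entering site as a covariate.

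The cost is a wording change and a few degrees of freedom. Site is already to be identified, so no new data are needed.
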